### Interim analyses

There will be six interim analyses, one after each of the six cohorts to determine which doses should be administered to each subsequent cohort of participants using a Bayesian model using all MMTT C-peptide measurements in all previous cohorts up to 12 months follow-up. Every cohort will have a placebo arm and a 2.5 mg/kg arm. Recruitment to the next cohort will not be halted and the DDC will be convened to determine the middle dose or doses (in the case of cohorts 2 and 3) to be applied to the next cohort. The trial statistician will produce a report with predictions from the Bayesian model to help recommend the next cohort’s middle dose selections for cohorts 2–7. The DDC will be required to come to a complete consensus for the middle dose(s) allocated to the next cohort combining clinical opinion, safety outcome information from the previous cohort’s data as well as the Bayesian model recommendations to make their decision. They will also examine CD4 + and CD8+T cell counts by dose to ensure that the dose is having some effect. If these levels do not change then that dose will not be allowed to be taken forward regardless of the recommendation of the Bayesian model. All safety outcomes by age will also be reviewed by the DDC as part of these interim analyses. The DDC and IDMC charter will expand on the above.

Specifically, the interim analyses will include an exploratory n sample decision to drop a dose/doses based on the CD4+/CD8 +T cell count ratio outcome at 1, 2, 4 and 12 weeks using a repeated measures model with fixed effects of dose and nominal days along with an interaction term between time and dose since randomisation. The mean differences between each dose level and placebo will be estimated with a 95% CI. CIs that indicate no change in CD4+/CD8 +T cell count ratio from baseline (ie, include 0) may indicate that this dose may be inactive and dropped from further cohorts.

These results will be used in conjunction with the C-peptide modelling which will be a Bayesian model of ln(AUC C-peptide +1). Only vague priors will be used in the model. The model will include fixed effects for categorical time and dose level along with an interaction term between time and dose and a random effect for participant. This model will be used to calculate the predictive probability that the mean ln(AUC C-peptide +1) is different from placebo for each dose level (including 2.5 mg/kg) given that the remaining participants to be allocated to the middle dose are given this dose level. If no such dose level is found then the next cohort of participants will be allocated to the 2.5 mg/kg dose level (improving power). Other stopping boundaries are not considered because the interim analyses are based on a mixture of incomplete follow-ups and fully observed follow-ups and subsequent analyses may suggest a middle dose not equal to 2.5 mg/kg. There is no sequential hypothesis testing done on the primary analysis.

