### Trial participants, study design and oversight

There will be continuous recruitment of 114 participants, divided into seven sequential cohorts with variable dose allocation.

The first cohort of 30 participants will be randomised to 5 intervention arms, namely placebo, 2.5 mg/kg, 1.5 mg/kg, 0.5 mg/kg and 0.1 mg/kg ATG total dose in a 1:1:1:1:1 allocation ratio stratified by two age groups 12–17 and 18–25. Recruitment will initially be limited to 12–25 year olds until the first 10 participants 12–17 years of age to receive a non-placebo dose of ATG have been observed for 4 weeks after last dose administration. For the age step-down, a dose determining committee (DDC) will examine the safety data in this initial group of 10 non-placebo dose participants 12–17 years of age and will determine whether it is safe to recruit younger participants (aged 5–11 years) into the trial. The independent data monitoring committee (IDMC) will review the DDC decision for the safety age step down analysis and will need to give final approval to allow the step down in age to occur.

The rationale for this step down is that ATG has not yet been used in this indication and at these doses in paediatric participants aged 5–11 years. New-onset T1D participants aged 12–45 were already treated with 2.5 mg/kg ATG in a previous clinical trial by Haller *et al* reported in 2018 and 2019 and and no concerning safety signals were seen in the 1 year trial with 5-year follow up.^25 26 29^

Once the age step-down has occurred, randomisation into cohort 1 will continue until 30 participants have been randomised, in a 1:1:1:1:1 allocation ratio within three age stratification groups (5–9, 10–17 and 18–25). After cohort 1 has been recruited, recruitment to cohort 2 will begin, including stratification to the three age groups (5–9, 10–17 and 18–25).

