As randomisation is stratified by the three age groups and as it is only balanced within each strata, once the step down in age has been achieved, there is a potential for some imbalance between intervention arms on the completion of each cohort dependent on the age distribution of the participants. According to the study power calculation, 32 participants on the placebo and 32 participants on 2.5 mg/kg ATG dose are required to achieve the desired power, therefore the DDC will ensure that enough participants are allocated to these two groups while trying to balance the three age groups in the stratified randomisation, as part of each DDC meeting convened after each cohort’s recruitment is completed. If there is an imbalance due to the age stratification within the randomisation the DDC will pick 2.5 mg/kg or placebo as the middle dose to ensure the power of the study; as we need to ensure that 32 participants are recruited to both the placebo and 2.5 mg/kg arm. This design allows sequential selection of the middle doses to be explored following review of all safety and early efficacy data by the IDMC and DDC to seek the minimum effective dose.

Potential participants will be identified by the clinical care teams at participating sites and will be approached by healthcare professionals and/or local research teams soon after T1D diagnosis. Potential eligible individuals or their parent/legal guardians (in case of children) will be provided with a verbal explanation of the study and applicable written participant information sheets (PISs). PISs will be translated into in the local language for the participating country. Once they have been given sufficient time to consider their participation in the trial, the participants/parents will be asked to provide written informed consent/assent to the study. Participants that withdraw from the trial after randomisation will not be replaced.

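### The exploratory interim dose-drop rule estimates a dose-versus-placebo difference in CD4+/CD8+ ratio but reads its confidence interval as change from baseline; with small arms the readings can give different recommendations

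*Protocol article*

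**What the plan says.** All of this is in the protocol article.

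- **Model (Interim analyses).** The exploratory dose-drop decision uses the "CD4+/CD8 +T cell count ratio outcome at 1, 2, 4 and 12 weeks using a repeated measures model". Its listed terms are dose, nominal days and their interaction.
- **Interval estimated.** "The mean differences between each dose level and placebo will be estimated with a 95% CI".
- **How the interval is read.** The following sentence turns to "CIs that indicate no change in CD4+/CD8 +T cell count ratio from baseline (ie, include 0"), and says that such intervals "may indicate that this dose may be inactive and dropped from further cohorts".
- **Companion rule on cell counts.** The paragraph before says that the Dose Determining Committee (DDC) looks at CD4+ and CD8+ counts by dose: "If these levels do not change then that dose will not be allowed to be taken forward regardless of the recommendation of the Bayesian model". This rule is repeated in Trial participants, study design and oversight. Neither place says what the change is measured against.
- **Size at the first interim.** "The first cohort of 30 participants will be randomised to 5 intervention arms", allocated equally. Because randomisation is balanced only within age strata, "there is a potential for some imbalance between intervention arms on the completion of each cohort".
- **Baseline data.** Table 1 (secondary objective 5) and Table 2 both schedule CD4/CD8 measurement at baseline.

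**The concern.** Two consecutive sentences give one interval two meanings. A difference from placebo and a change from baseline are different estimands with different standard errors and different biases.

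- A difference from placebo in post-treatment values is controlled by randomisation but carries the full between-person spread.
- A within-arm change removes the stable part of that spread but has no control for anything that moves the ratio in every arm. Such a common movement is plausible: corticosteroid premedication is recommended, and the Placebo section says premedication requirements are the same for placebo.
- The difference from placebo in change lies between the two in precision and keeps the control.

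An analyst preparing the first report to the DDC could follow either sentence. What is at stake is which doses are recommended for later cohorts, and so how many participants each middle dose has at the final test.

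**Working it through.** **Plan's own figure.** The rule states no operating characteristic, so there is none to reproduce. The 32 per arm in the sample size section concerns C-peptide and does not enter here.

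**Inputs from the document.** Cohort 1 has 30 participants over 5 arms, so n = 30/5 = 6 per arm as planned. The interval is 95%, and covering 0 is the signal to consider dropping.

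**Assumptions.** The article gives no SD, correlation or effect for the ratio. I work in units of the between-person SD, with normal data, equal variances and one visit. The true shift in the dose arm is 0.8 SD with none on placebo, and the baseline to follow-up correlation r is 0.6, 0.8 or 0.9.

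**Standard errors at n = 6**

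- Post-treatment difference from placebo: sqrt(2/6) = 0.577, 10 df.
- Within-arm change from baseline: sqrt(2(1 − r)/6), which is 0.258 at r = 0.8, 5 df.
- Difference from placebo in change: sqrt(4(1 − r)/6), which is 0.365 at r = 0.8, 10 df.

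**Probability that the interval covers 0.** With non-centrality λ = shift/SE, this is P(|T| < t₀.₉₇₅) for T non-central t. At r = 0.8, λ = 0.8/0.577 = 1.39, 0.8/0.258 = 3.10 and 0.8/0.365 = 2.19.

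| r | Post-treatment difference | Within-arm change | Difference in change |
|---|---|---|---|
| 0.6 | 76% | 57% | 71% |
| 0.8 | 76% | 30% | 49% |
| 0.9 | 76% | 7% | 20% |

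Pooling the variance over the five arms (25 df) leaves the pattern in place: 73%, 15% and 44% at r = 0.8.

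**Sensitivity to the shift.** At r = 0.8 a 2 SD shift gives 12%, under 0.1% and 0.2%. At 3 SD all three are below 0.5%.

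**Disagreement on the same data.** A simulation with n = 6, r = 0.7 and a shift of 1 SD in the dose arm only (60,000 runs) had the interval excluding 0 in 72% of runs for within-arm change, 52% for difference in change and 35% for post-treatment difference. The within-arm reading disagreed with the other two in 29% and 51% of runs respectively.

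**The opposite error.** Suppose both arms shift by 0.5 SD, so the dose has no effect over placebo. The within-arm interval then excludes 0, and the dose looks active, in 20%, 35% and 60% of trials at r = 0.6, 0.8 and 0.9. Either placebo contrast does so in 5%.

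**The case against.** **The second sentence is shorthand.** The only interval specified is a contrast with placebo, so the natural repair is that the response is change from baseline, compared with placebo. The within-arm figures then fall away, and the remaining ambiguity is 76% against 49% at r = 0.8, or only 76% against 71% at r = 0.6. This is a fair reading, but the text does not state it. Even under it, an interval covering 0 means no difference from placebo, so the sentence would still misdescribe the result.

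**The article is condensed.** The section says that the DDC and independent data monitoring committee charter will expand on it, and whether baseline enters the model could be left there. I accept that an unlisted baseline term would not be a finding by itself. The finding is that two stated sentences conflict. The section on the primary analysis does name a baseline covariate, so its absence here cannot simply be presumed an abbreviation. The statistical analysis plan is promised only before the final database lock, which may be after the interim decisions.

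**The figures are selective.** They rest on an assumed shift, one visit and the first interim's planned size. The planned model uses four visits, and later interims accumulate cohorts. That stands: the figures show that the readings can diverge, not how often they will.

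**Two stronger inferences do not hold.** A reader might infer that an interval covering 0 removes a dose whatever the Bayesian model says. The mandatory wording attaches to the DDC's check of CD4+ and CD8+ counts. The interval rule for the ratio is called exploratory and says only that a dose may be inactive, and the DDC decides by consensus on several sources. A reader might also infer that a dropped dose can never be declared the minimally effective dose. The section on primary analyses compares every other dose level with placebo if 2.5 mg/kg succeeds, so a dropped dose keeps the participants it has and is still tested, with less power.

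**Conclusion.** The inconsistency is real and nothing else in the article resolves it: a dose-placebo interval is read as evidence about change from baseline. With about 6 per arm and a moderate effect, the choice of reading can alter the drop recommendation. At an assumed 0.8 SD shift the chance that the interval covers 0 spans 57% to 76% at correlation 0.6 and 7% to 76% at 0.9. At 2 SD and correlation 0.8 the largest gap is about 12 percentage points, and by 3 SD it has gone. All of this depends on a shift and correlation that the article does not supply.

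The consequence is limited to advice to the DDC on which doses receive further participants, and hence the power of those comparisons. The primary contrast, its sample size and the planned final testing sequence are untouched. It is a wording defect in a stated decision rule, worth correcting because the correction costs almost nothing.

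**What to change.** 1. Use one quantity in both sentences: the dose-minus-placebo difference in CD4+/CD8+ ratio, adjusted for the baseline ratio, from the planned repeated-measures model over its four visits.
2. Replace the phrase about no change from baseline with: no difference from placebo, adjusted for baseline.
3. Add the baseline ratio to the listed model terms. Ignoring the estimation of one slope, the baseline-adjusted variance is 2(1 − r²)/6. This is no larger than the 4(1 − r)/6 for the difference in change, because 1 + r ≤ 2.
4. State the same comparator for the rule about cell-count levels not changing, in both Interim analyses and Trial participants, study design and oversight, so that the mandatory count check and the exploratory ratio check can be reconciled.

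The cost is a few words in the protocol and the charter. Baseline CD4/CD8 is already scheduled, so no samples or visits are added. Nothing here bears on which doses should be chosen.

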Cohort 2 will consist of 12 participants randomised to 4 intervention arms, placebo, ATG 2.5 mg/kg and two middle ATG doses, in a 1:1:1:1 allocation ratio stratified by the three age groups. The choice of the middle doses will be made by the DDC using all available clinical, mechanistic and safety data from the previous cohort’s data. Further a Bayesian model’s predictions, using all MMTT C-peptide measurements in cohort 1 up to 12 months follow-up, will be used to help recommend cohort 2’s middle dose selections to the DDC. CD4 + and CD8+T cell counts will also be used for the DDC’s decision because as shown by Haller *et al*^26^ they represent an effectivity indicator for dose action: If these levels do not change then that dose will not be allowed to be taken forward regardless of the recommendation of the Bayesian model. The DDC will be required to come to a complete consensus for the middle dose(s) allocated to the next cohort. After cohort 2 has been recruited, recruitment to cohort 3 will begin.

Cohort 3 will consist of 12 participants randomised to 4 intervention arms, placebo, 2.5 mg/kg ATG and two middle doses decided by the DDC, in a 1:1:1:1 allocation ratio stratified by the three age groups. The DDC will be convened to determine the two middle doses to be applied to cohort 3 following the same procedure as described above, using all MMTT C-peptide measurements for all participants in all previous cohorts up to 12 months follow-up. The middle doses selected for cohort 3, or indeed any future cohorts, may be different to those selected for cohort 2, or previous cohorts. After cohort 3 has been recruited, recruitment to cohort 4 will begin.

Cohort 4 will consist of 15 participants randomised to 3 intervention arms, placebo, 2.5 mg/kg ATG and a single selected middle dose decided by the DDC, in a 1:1:1 allocation ratio stratified by the three age groups. The DDC will again be convened to determine the one middle dose to be used in cohort 4, following the same procedure as described above.

Cohorts 5, 6 and 7 will each consist of 15 participants randomised to three intervention arms, placebo, 2.5 mg/kg and selected middle doses, in a 1:1:1 allocation ratio within each age group. The above-described process will continue for each cohort up to Cohort 7 with additional individual interim analyses to identify the middle doses to be used in cohorts 5–7.

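### The interim dose score has no direction, so a dose that looks worse than placebo scores as well as one that looks equally better

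*Protocol article*

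**What the plan says.** All of this is in the protocol article.

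- **Score** (Interim analyses): "This model will be used to calculate the predictive probability that the mean ln(AUC C-peptide +1) is different from placebo for each dose level". It is computed "given that the remaining participants to be allocated to the middle dose are given this dose level".
- **Prior:** "Only vague priors will be used in the model".
- **Fallback:** "If no such dose level is found then the next cohort of participants will be allocated to the 2.5 mg/kg dose level". The article gives no probability cut-off for this branch.
- **Cohort sizes** (Trial participants, study design and oversight): "The first cohort of 30 participants will be randomised to 5 intervention arms", "Cohort 2 will consist of 12 participants randomised to 4 intervention arms" and "Cohorts 5, 6 and 7 will each consist of 15 participants randomised to three intervention arms".
- **Who decides** (Interim analyses): the trial statistician's report helps to recommend the middle doses. The DDC must reach full consensus, weighing clinical opinion, safety and the model. A dose with no change in CD4 and CD8 counts is barred whatever the model says. A DDC and independent data monitoring committee (IDMC) charter is to give more detail.
- **Sidedness** (sample size section): tests are described as superiority tests and as two-sided.

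**The concern.** The purpose of choosing middle doses adaptively is directional: the trial looks for the smallest dose that preserves C-peptide. The score is not. A probability of being *different* adds the chance of ending significantly above placebo to the chance of ending significantly below it.

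At a final test this does little damage, because the sign of the estimate is read alongside the p-value. In a score that ranks doses for the next cohort it does matter. A dose whose early data point downwards can be put ahead of one whose data point modestly upwards.

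Middle-dose places are scarce: 3 per dose in cohorts 2 and 3, and 5 per cohort from cohort 4. Places spent on the wrong dose cannot be recovered, and they reduce the power to identify a minimally effective dose.

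**Working it through.** **Inputs.** SD 0.27 on the transformed scale, from the sample size section. First interim: 30 over 5 arms = 6 per arm. Final placebo arm: 6 + 3 + 3 + 4×5 = 32. Vague prior, taken as flat. Two assumptions: 12-month data are complete at the interim, and the dose being scored also ends with 32.

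**The plan's own figure.** n = 2(1.96 + 1.282)² × 0.27²/0.22² = 31.7, so 32 per arm, as stated.

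**Formula.** *Different* is read as a final two-sided test significant at 5%. Given an interim difference d, the final estimate is Normal with mean d and variance vi − vf.

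- vi = 0.27²(1/6 + 1/6) = 0.0243
- vf = 0.27²(1/32 + 1/32) = 0.00456
- predictive SD = √(0.0243 − 0.00456) = 0.1405
- significance threshold = 1.96 × √0.00456 = 0.1323

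**Score by observed difference.**

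| d | Upper tail (higher) | Lower tail (lower) | Score (different) |
|---|---|---|---|
| −0.22 | 0.006 | 0.734 | 0.74 |
| −0.20 | 0.009 | 0.685 | 0.69 |
| 0 | 0.173 | 0.173 | 0.346 |
| +0.20 | 0.685 | 0.009 | 0.69 |
| +0.22 | 0.734 | 0.006 | 0.74 |

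For example, at d = +0.20 the upper tail is Φ((0.20 − 0.1323)/0.1405) = Φ(0.482) = 0.685. The lower tail is Φ((−0.1323 − 0.20)/0.1405) = Φ(−2.365) = 0.009.

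**Floor.** The minimum, 0.346, occurs at d = 0. It does not depend on the SD, which cancels. It is 0.371 if the dose ends with 38 (its 6 plus all 32 remaining middle-dose places) and 0.34 if the variance is treated as unknown. It falls to 0.22 at 9 per arm, 0.13 at 12, 0.04 at 17 and 0.004 at 22. If incomplete follow-up leaves information worth only 3 per arm (an assumption), it rises to 0.53. The symmetry does not fade with accrual.

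**Ranking at the first interim.** Simulated with three middle doses sharing one placebo arm and no cut-off involved.

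| Truth | Result | Different | Higher |
|---|---|---|---|
| All three null | Top-ranked dose has a negative estimate | 50% | – |
| One dose +0.2, two null | Effective dose ranked first | 61% | 83% |
| One +0.2, one null, one −0.2 | Effective dose ranked first | 46% | 90% |

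**Fallback at the first interim, by assumed cut-off.**

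| Cut-off | Fallback, all null: different | Fallback, all null: higher | True +0.2 dose missed: higher |
|---|---|---|---|
| 0.34 | 0% | 45% | – |
| 0.5 | 22% | 61% | 33% |
| 0.7 | 58% | 79% | 52% |
| 0.8 | 74% | 87% | – |
| 0.9 | 89% | 94% | – |

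**The case against.** **The fallback.** A reader might infer that a floor of 0.35 disables the fallback in the early cohorts, so that an ineffective dose is always taken forward. The documents do not support this. It holds only for a cut-off below about 0.35, and the article states none. With high cut-offs the fallback fires in most all-null first interims. The cut-off may be set in the statistical analysis plan or the charter, neither of which is shown, so its absence is not a finding.

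**Who allocates.** A reader might also infer that the score decides which doses receive participants. It does not: it is one input to a committee that must agree fully, that reviews safety, and that must bar a dose without CD4/CD8 change. The simulations model none of this. That limits the harm but leaves the score uncorrected. The CD4/CD8 bar screens out biological inactivity. It does not screen out a dose that changes T cells without helping C-peptide. The committee may well notice a negative estimate, but then it is working around the number it was given.

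**The literal reading.** In a continuous model two means differ with probability 1, so on the literal wording no dose could fail. That reading is not fair to the text. The score is conditional on where the remaining participants go, so it plainly refers to the end-of-trial comparison.

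**The wording.** *Different* follows the primary objective, which defines the minimally effective dose as significantly different from placebo, and the two-sided tests. That explains the word. It does not make it suitable for a ranking.

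**Assumed harm.** The documents give no evidence that doses below 2.5 mg/kg lower C-peptide. This is fair, and it is why the 61% against 83% result uses no harmful dose. Cohorts 2 and 3 each carry two middle doses, so being ranked first is a summary of the score's quality there and not the exact decision.

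**Conclusion.** The concern holds in a limited form. The interim score as written gives apparent harm the same credit as apparent benefit, 0.69 at both −0.20 and +0.20 at the first interim. It therefore ranks a truly effective dose first less often than it could, 61% against 83% when the other two are null. Neither result depends on a cut-off, and the second assumes no harmful dose.

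The figures rest on 6 per arm, 32 v 32 at the end, SD 0.27, a flat prior, complete 12-month data and a normal approximation. The floor of about 0.35 is a problem of the early interims and is small from about 17 per arm, although a dose not used again stays at 6.

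The final test and its type I error are outside this point. What is affected is the quality of advice to the DDC. It is worth correcting because the correction is nearly free.

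**What to change.** In the Interim analyses section, define the score as the predictive probability that the final 12-month comparison shows the dose significantly higher than placebo on ln(AUC C-peptide + 1), counting the upper tail only.

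Apply whatever cut-off the statistical analysis plan or charter uses for the fallback to this directional score, and check it by simulation at 6 per arm. The check should weigh how often the fallback fires when no middle dose works against how often an effective dose is passed over. As the working shows, those two pull against each other: at 0.5 the fallback fires in 61% of all-null first interims, but a true 0.2 effect is missed in 33%. A strict cut-off is therefore not harmless this early, although later interims may select a different dose.

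Cost: a few words in the protocol and charter, one line in the interim program and a small simulation. The final analysis is unchanged.
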